## Abstract

**Background:**

To achieve potential financial savings and avoid exposing the patients to unnecessary risk, an optimal diagnostic strategy to identify low risk individual who may derive minimal benefit from further cardiac imaging testing (CIT) is important for patients with stable chest pain (SCP) suggestive of chronic coronary syndrome (CCS). Although several diagnostic strategies have been recommended by the most recent guidelines, few randomized controlled trials (RCTs) have prospectively investigated the actual effect of applying these strategies in clinical practice.

**Methods:**

OPERATE (**OP**timal **E**valuation of stable chest pain to **R**educe unnecess**A**ry utilization of cardiac imaging **TE**sting) trial is an investigator-initiated, multicenter, coronary computed tomography angiography (CCTA)-based, 2-arm parallel-group, double-blind, pragmatic and confirmative RCT planning to include 800 subjects with SCP suggestive of CCS. After enrollment, all subjects will be randomized to two arms (2016 U.K. National Institute of Health and Care Excellence guideline-determined and 2019 European Society of Cardiology guideline-determined diagnostic strategy) on a 1:1 basis. According to each strategy, CCTA should be referred and deferred for a subject in high and low risk group, respectively. The primary (effectiveness) endpoint is CCTA without obstructive coronary artery disease. Safety of each strategy will be mainly assessed by 1-year major adverse cardiovascular event rates.

**Discussion:**

The OPERATE trial will provide comparative effectiveness and safety evidences for two different diagnostic strategies for patients with SCP suggestive of CCS, with the intension of improving the diagnostic yield of CCTA at no expense of safety.

**Clinical trial registration:**

ClinicalTrial.org Identifier NCT05640752.

**Supplementary Information:**

The online version contains supplementary material available at 10.1186/s12872-023-03424-3.

## Background

In daily clinical routine, the evaluation of new-onset stable chest pain (SCP) suggestive of chronic coronary syndrome (CCS) remains a challenge for physicians, in consideration of the decreasing prevalence of coronary artery disease (CAD) and dramatically rising costs related to these patients [1, 2]. Although coronary computed tomography angiography (CCTA) has been the first-line cardiac imaging testing (CIT) according to current recommendations [3–5], an increasing body of evidence pointed to the fact that most of patients referred to CCTA as well as other CIT had normal results and no adverse clinical events [6–10]. Thus, an optimal diagnostic strategy to identify low risk patients who may derive minimal benefit from further CIT is the cornerstone of clinical management for SCP, which has been proposed and reiterated by most recent guidelines to achieve potential financial savings and avoid exposing patients to unnecessary risk [3–5].

Different diagnostic strategies have been developed to defer unnecessary CIT. The 2016 U.K. National Institute of Health and Care Excellence (NICE) guideline abandoned pretest probability (PTP)-based strategy and recommended the referrals of CCTA in patients with angina or abnormal ECG [5]. On the contrary, the 2019 European Society of Cardiology (ESC) guideline suggested an updated PTP model to rule out CAD in patients with ESC-PTP ≤ 5% and recommended noninvasive CIT for patients with ESC-PTP ≥ 5% [3]. For patients with borderline ESC-PTP (5–15%), Winther et al. developed the risk factor-weighted clinical likelihood (RF-CL) model, which was also proven to improve the prediction of CAD [11]. Both ESC-PTP and RF-CL model were recommended by the latest guideline for evaluation and diagnosis of chest pain [4].

2016 NICE guideline-determined diagnostic strategy (NICE strategy) [12, 13] and ESC guideline-determined diagnostic strategy (ESC strategy) [11, 14, 15] were externally validated and compared in different CCTA-based cohorts of SCP patients, as well as our previous studies from the CCTA Improves Clinical Management of Stable Chest Pain (CICM-SCP) registry [16–18]. While evidences from these observational cohorts and post hoc analyses of randomized controlled trial (RCT) suggested that the PTP-based strategy offered more effective deferral for CIT than the symptom-focused strategy did [16], they only examined patients who had underwent CIT and indications for CIT relied on a nonrandomized and complicated fashion, resulting in substantial biases. In fact, few RCTs have prospectively determined the actual effect of applying these strategies in clinical practice [19, 20].

Therefore, the OPERATE (**OP**timal **E**valuation of stable chest pain to **R**educe unnecess**A**ry utilization of cardiac imaging **TE**sting) study is designed to compare the effectiveness and safety of two proposed diagnostic strategies, ESC and NICE strategy, in identification of low risk individual who may derive minimal benefit from CCTA among patients with SCP suggestive of CCS in a pragmatic RCT.

## Methods/design

### Overall design and objectives

Figure 1 shows an overview of the study design. OPERATE trial is an investigator-initiated, multicenter, CCTA-based, 2-arm 1:1 parallel-group, double-blind, pragmatic and confirmative RCT planning to include 800 subjects with SCP suggestive of CCS (ClinicalTrials.gov Identifier NCT05640752). This study protocol is developed in accordance with the Standard Protocol Items: Recommendations for Interventional Trials (SPIRIT) [21] and the SPIRIT checklist is available in Additional file 1. The primary objective of OPERATE trial is to compare the rates of CCTA without obstructive CAD according to NICE and ESC strategy. The key secondary objective is to assess whether the two strategies have no significant difference in terms of major adverse cardiac events (MACEs). We hypothesize that when comparing with NICE strategy, ESC strategy which sequentially incorporated the ESC-PTP model with RF-CL model will decrease the probability of CCTA without obstructive CAD but not at the expense of safety and cost over a follow-up period of 1 year.

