For each subject, ESC-PTP is calculated using age, sex and type of chest pain according to 2019 ESC guideline for the diagnosis and management of CCS [3] and RF-CL is calculated using age, sex, type of chest pain, hypertension, dyslipidemia, diabetes, smoking and family history of CAD based on the publication of Winther et al. [11], respectively. According to ESC strategy, subjects with ESC-PTP ≤ 5% are classified into low risk group and ones with ESC-PTP ≥ 15% are classified into high risk group [3]. For subjects with ESC-PTP of 5-15%, ones with RF-CL ≥ 15% are classified into high risk group and ones with RF-CL < 15% are classified into low risk group. The cut-off of 15% for RF-CL is chosen because RF-CL < 15% was associated with an extremely low prevalence of obstructive CAD and risk of clinical events [11, 16].

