### Study endpoint

The primary outcome, main secondary outcomes and other outcomes are described below and all outcomes are included Table 3. The primary endpoint of the study which indicates effectiveness of the diagnostic strategy is CCTA without obstructive CAD, defined as the summary of nonobstructive CAD, no sign of CAD and nondiagnostic result detected by CCTA according to each strategy during initial management. Obstructive CAD is defined as present if a patient had at least one lesion with ≥ 50% diameter stenosis at CCTA.

**Table 3 Tab3:** Study endpoints

Outcome	Topic	Description
Primary	CCTA without obstructive CAD	Summary of nonobstructive CAD, no sign of CAD and nondiagnostic result on CCTA during initial management
Secondary		
Safety	MACE	Composite of death, nonfatal MI and hospitalization due to unstable angina
	Individual cardiovascular endpoint	All-cause death, nonfatal MI and hospitalization due to unstable angina, respectively
	Exposure to radiation	Cumulative estimated radiation exposure related to cardiovascular care during the whole study period
	Procedural complications	Major: renal failure, stroke, severe bleeding and anaphylaxis or other complications if they lead to a hospital stay of at least 24 h Minor: complications not leading to prolonged stay, such as slight decrease of renal function, anaphylaxis and bleeding
Effectiveness	No. of cardiovascular procedures	Noninvasive CIT: exercise ECG, CCTA, PET-CT, MRI, myocardial perfusion imaging and stress echocardiography Invasive procedures: ICA and CR (CABG and PCI)
	Diagnostic metrics of CCTA during initial management	
	Diagnostic yield	No. of obstructive CAD/No. of CCTA×100%
	Proportion of necessary CCTA	No. of necessary CCTA/No. of CCTA×100%
	Proportion of normal CCTA	No. of normal CCTA/No. of CCTA×100%
	Other outcomes	HRQOL: Seattle Angina Questionnaire and visual-analogue scale of the European Quality of Life–5 Dimensions Time length of initial management: from successful eligibility to the end of initial management

CIT: cardiac imaging testing; MI: myocardial infarction; ECG: electrocardiogram; CR: coronary revascularization; HRQOL: health-related quality of life; MACE: major adverse cardiovascular events; CCTA: coronary computed tomography angiography; PET-CT: positron emission tomography-CT; MRI: magnetic resonance imaging; ICA: invasive coronary angiography; CABG: coronary artery bypass grafting; PCI: percutaneous coronary intervention

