### Sample size

The sample size calculation is performed using R (version 3.6.4; R Foundation for Statistical Computing, Vienna, Austria). To compute a weighted average rate as the projected rate of CCTA without obstructive CAD for a diagnostic strategy, data from previous literatures used in the sample size calculation include rate of CCTA without obstructive CAD in high risk group and distribution of subjects in low and high risk group.

For NICE strategy, theses parameters fluctuated over a wide range in different cohorts [12, 13, 16]. Thus, the distribution of subjects and the rate of CCTA without obstructive CAD in high risk group is estimated to be approximately 2:3 for low/high risk group and 62%, respectively, resulting in a projected rate of 3/(2 + 3)×57%=37.2%. Similarly, we assume that the projected rate of primary endpoint is 2/(2 + 3)×57%=22.8% for ESC strategy, based on the results of the original study [11] as well as our previous studies including one which investigated the RF-CL model in subjects with borderline PTP [16, 17].

For the analysis of primary endpoint, on 2-sided test 5% significance level and for the 1:1 allocation ratio, a sample size of 800 (allowing for 10% noncompletion) will provide more than 99% power between NICE and ESC arm. Thus, the final sample size is chosen to be 800 subjects (400 in each randomization group).

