### Statistical plan

All statistical analyses are performed by the statistical and data coordinating group using R (version 3.6.4; R Foundation for Statistical Computing, Vienna, Austria) or MedCalc (version 15.2.2; MedCalc Software, Mariakerke, Belgium). Two-tailed P < 0.05 is considered statistically significant. The primary analysis is conducted according to a modified intention-to-treat (ITT) principle. All subjects who undergone randomization and don’t withdraw before assigned intervention (CCTA or no further testing) or other CIT during the initial management will be included. Categorical variables will be described by counts and proportions and compared by chi-square tests or fisher exact test. Continuous variables will be described by mean and standard deviation or median and interquartile range and compared through t test or Mann-Whitney U tests.

The comparison of primary outcome between two diagnostic strategy regimens was expressed as risk ratio, along with 95% confidence interval and number needed to treat. The per-protocol analysis excluding subjects with insufficient compliance or with other major protocol deviation(s) and the traditional ITT analysis including all subjects who are randomized will be performed as prespecified sensitivity analyses. Different diagnostic metrics, such as initial CIT without positive result, unnecessary CCTA and CCTA with no sign of CAD, will also be considered as sensitivity analyses. To explore the consistency of strategy effectiveness according to specific subject characteristics, a limited number of prespecified subgroup analyses for the primary endpoint are conducted using interaction terms in log-binomial regression models. We will also undertake a hierarchical analysis (giving priority to clinical importance of the components of the composite outcome rather than time to first event: Death > nonfatal MI > hospitalization due to unstable angina > CCTA without obstructive CAD > referral to CIT) using the matched win ratio method [35].

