The risk of incorrectly deferral of CIT for patients with severe CAD should emerge as particularly strong candidates accounting for the overuse of CIT in clinical practice [1]. In fact, a risk of false negative will always be present for any testing and current guidelines recommended no further CIT in patients with low probability of obstructive CAD and cardiovascular events [3–5]. Thereby, identifying a proportion of patients at low risk to avoid CIT which may lead to false positive results and extra exposure of accompanying risk is acceptable, especially in an era of excess CIT use [42]. Data from more than 30, 000 CCS patients demonstrated that on the basis of contemporary OMT, most patients with angina were likely to experience resolution of symptoms without events or CR [43]. Moreover, both NICE and ESC strategy were externally validated in the CICM-SCP registry composed of patients from similar sites [16–18], which maximized the generalizabilities and reliabilities of them. Indeed, according to data from CICM-SCP registry composed of patients who underwent CCTA based on the decisions of local physicians, the proportion of patients who were classified into low risk group by NICE and ESC strategy but suffered MACE during a 17-month follow-up was only 1.1% and 0.7%, respectively [16]. On the other hand, the principle of OPERATE trial which left major decisions to local heart team members and referring physicians is intended to allow considerable leeway for clinical judgment in keeping with the pragmatic design. Also, this design in combination with ITT analysis can potentially elucidate the effectiveness of diagnostic strategies in routine clinical practice.

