Several representative RCTs [7, 9, 48, 49] and observational registry [16, 43] has provided obvious evidences that patients referred to CIT for suspected CCS had a very low rate of clinical event, resulting in a urgent demand to conservatively improve utilization of resources [1]. Meanwhile, the low event rate will limit our strength of evidence and causal statements inferred from an underpowered trial with a predefined primary outcome of MACE [1, 27]. To overcome this problem, we choose CCTA without obstructive CAD as primary endpoint to indicate effectiveness of the diagnostic strategy, which is, in turn, the main concerned outcome of PTP models, and introduce the approach of win ratio to analyze composite endpoint of MACE, CCTA without obstructive CAD and referral to CIT in the order of clinically importance. Similar designs using the imaging-based primary endpoints have also been selected by other comparative effectiveness trials of diagnostic strategies for SCP [20, 32, 50]. In addition, although it has been proposed that cardiac ischemia or plaque characteristics detected by CCTA to target intervention may improve clinical outcome, a detailed evaluation and treatment pathway have not been established [32, 51, 52]. Thus, anatomy severity remains the primary arbiter of post-CCTA management [4].

In patients with SCP suggestive of CCS, CCTA provided excellent performance for diagnoses and prognosis of CAD in a noninvasive and feasible way [27] and major guideline bodies have started to endorse incorporation of CCTA more definitively than before [3–5, 28]. Thus, we uniformly give CCTA the first-line status in subjects at high risk according to NICE and ESC strategy for several reasons. First, recent researches indicated that in terms of major clinical outcomes, CCTA-first strategy was superior or not inferior to NFT- or ICA-first strategy [7, 9, 49, 53, 54]. Second, CCTA are broadly available because of relatively low technical and personnel demands, while NFT, like positron emission tomography and stress cardiac magnetic resonance, although powerful, are much less available and their applicability is still limited by infrastructural and capacity requirements, especially in China [10]. Third, models constituting the ESC strategy were established in CCTA-based cohorts [3, 11]. Last, the post-CCTA clinical management paradigm based on CAD-RADS has been demonstrated to be associated with lower risk of MACEs and fewer invasive procedures [30].

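### The MACE safety objective is framed as finding no significant difference, with no margin or confidence-interval criterion, and the detection metrics are per CCTA only, so a non-significant result cannot support the safety half of the hypothesis

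*Protocol article*

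**What the plan says.** Under Overall design and objectives, the Protocol article hypothesises that the ESC strategy lowers the primary endpoint "but not at the expense of safety and cost over a follow-up period of 1 year". The key secondary objective meant to support the safety part is to "assess whether the two strategies have no significant difference in terms of major adverse cardiac events (MACEs"). Study endpoint makes time to first MACE the key secondary endpoint.

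The Statistical plan sets one general criterion, "Two-tailed P < 0.05 is considered statistically significant", and for time-to-event endpoints gives Kaplan-Meier curves, a log-rank P value and an adjusted Cox model. No acceptable excess risk, non-inferiority margin or confidence-bound rule appears. Sample size is worked out for the primary endpoint only, "on 2-sided test 5% significance level and for the 1:1 allocation ratio".

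The Discussion remarks that "the low event rate will limit our strength of evidence and causal statements inferred from an underpowered trial", and the sentence goes on to specify a trial with MACE as its predefined primary outcome. The only MACE rates in the document are registry figures for patients whom NICE and ESC classified as low risk and who "suffered MACE during a 17-month follow-up was only 1.1% and 0.7%, respectively".

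On detection, Table 3 defines diagnostic yield as "No. of obstructive CAD/No. of CCTA×100" (a percentage). The proportions of necessary and normal CCTA have the same denominator.

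**The concern.** Failing to find a significant difference is not evidence that two strategies are similarly safe. The fewer the events, the more likely a non-significant P value becomes, whatever the true effect. An objective worded this way invites a small trial to report safety it has not shown.

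The endpoints add a second blind spot. A deferred subject cannot have the primary event at initial management, and the yield metrics count only those scanned. A strategy that scans fewer people can therefore look better on the primary endpoint and on yield while finding fewer cases of obstructive CAD among everyone randomised. Half of the stated hypothesis depends on measures that cannot settle it.

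**Working it through.** **1. The plan's own power figure.** Inputs from Sample size: 37.2% (NICE) against 22.8% (ESC), two-sided 5%, 400 per arm, 10% noncompletion. The 37.2% equals 3/5 × 62%; the 57% printed in that formula would give 34.2%, so I use 62%. A pooled two-proportion test gives power of 99.4% at 400 per arm and 98.9% at 360. The stated figure of over 99% reproduces at full enrolment and is only marginally missed after noncompletion. It concerns the primary endpoint and says nothing about MACE.

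**2. MACE events (assumed).** I take 1-2% at 1 year as an assumption and extend it to 3%: 800 × 1% = 8, 800 × 1.5% = 12, 800 × 2% = 16, 800 × 3% = 24.

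**3. Log-rank power for a hazard ratio of 2.** With D total events and 1:1 allocation, power = Φ(½√D × ln 2 − 1.96). For D = 8: ½ × 2.828 × 0.693 − 1.96 = −0.98, so 16%. The smallest observed hazard ratio that reaches significance is about exp(1.96 × 2/√D).

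| Events | Power, HR 2 | True doubling non-significant | Smallest significant HR |
|---|---|---|---|
| 8 | 16% | 84% | 4.0 |
| 12 | 22% | 78% | 3.1 |
| 16 | 28% | 72% | 2.7 |
| 24 | 40% | 60% | 2.2 |

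For 80% power, D = 4 × (1.96 + 0.842)² / (ln 2)² = 65.3, so 66 events.

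**4. What a confidence interval could show at 400 per arm.** Half-width for the risk difference = 1.96 × √(2p(1−p)/400): 1.4 points at p = 1% and 1.9 points at p = 2%. With no true difference and p = 2%, the standard error is 0.99 points. The chance that the upper bound excludes an excess of m points is Φ(m/0.99 − 1.96): 17% for 1 point, 52% for 2 points, 86% for 3 points. For 80% power (one-sided 2.5%), a 1-point margin needs 1,555 per arm at 1% and 3,077 at 2%; a 2-point margin needs 389 and 770. These margins are illustrations; the document gives none.

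**5. Detection per randomised subject.** Assume every high-risk subject and no low-risk subject is scanned.
- NICE: 60% × (100% − 62%) = 60% × 38% = 22.8%, about 91 of 400.
- ESC: 40% × (100% − 57%) = 40% × 43% = 17.2%, about 69 of 400.
- Yield per CCTA: 38% against 43%, favouring ESC.
- Found per randomised subject: 22.8% − 17.2% = 5.6 points fewer under ESC, about 22 per 400. The 95% half-width is 1.96 × √(0.228 × 0.772/400 + 0.172 × 0.828/400) = 5.5 points.

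The two ways of counting point in opposite directions.

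**6. Sensitivity of step 5.** With illustrative inputs of 55% × 35% = 19.25% for NICE and 45% × 43% = 19.35% for ESC, the gap vanishes (−0.1 points). The direction depends on the inputs; the dependence on the denominator does not.

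**The case against.** No sentence in the article says that P above 0.05 will be declared safe. The objective is to assess, and Kaplan-Meier curves, a Cox model, the individual MACE components, radiation and complications are also planned. This stands: the decision rule is implied by the wording and is not printed. But the wording is all the reader has, and nothing else in the article says what result would support the safety claim. Leaving detail to an analysis plan does not resolve it, because the objective itself is fixed in terms of significance.

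The Discussion is open about low event rates. A reader might infer that the sponsor concedes MACE cannot be analysed. It does not: the sentence explains why MACE was not made primary. Its remedies are an imaging primary endpoint and a win ratio, and neither changes how the safety objective is judged. With 16 events, at most 16 of 400 matched pairs (4%) can be decided on a MACE tier, so the win ratio would rest mainly on the CCTA and referral tiers below.

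The event count is assumed. The registry rates cover low-risk patients over 17 months, whereas the trial also enrols high-risk subjects. This stands too, but the conclusion survives at 24 events.

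Detection per randomised subject can be derived from listed items (number of CCTAs less primary events), and deferred subjects whose symptoms persist may be tested later. Both are true. Disease not found at initial management is therefore not necessarily missed, and the request is for explicit reporting.

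**Conclusion.** The concern holds in two parts. First, the safety objective is framed so that a non-significant MACE comparison would stand as support for safety, with no margin, confidence-bound criterion or MACE power behind it. Under an assumed 1-2% event rate, a true doubling of hazard would go undetected about 72-84% of the time, and about 60% even with 24 events. Second, no listed endpoint gives obstructive CAD detected per randomised subject, and the per-CCTA metrics can move the opposite way. The primary analysis and its power are unaffected.

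A reader might go further and divide the 5.6-point gap by the 60% whom ESC defers, obtain 9.3%, and set this against the statement that "RF-CL < 15% was associated with an extremely low prevalence of obstructive CAD and risk of clinical events". The documents do not support that contradiction. The planning inputs are rounded, come from different source cohorts, and vary widely for NICE by the protocol's own account, so 9.3% is not a minimum prevalence. The quoted statement also covers only RF-CL below 15%, not all ESC-deferred subjects. The 22.8% and 17.2% show what the denominator does; they do not forecast missed disease.

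**What to change.** Replace the no-significant-difference objective with estimation of the 1-year Kaplan-Meier MACE risk difference (ESC minus NICE) and its two-sided 95% CI. Then choose one of two routes in advance:

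- State and justify a margin, and claim that safety is not compromised only if the upper bound lies below it. Otherwise report the result as inconclusive.
- Declare MACE descriptive, report the estimate and interval, and make no safety claim.

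Add obstructive CAD detected per randomised subject, with the between-arm difference and 95% CI, beside the primary endpoint and the per-CCTA yield.

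The cost is wording in the protocol and analysis plan; the trial already plans to collect these data. The real downside is that, at 400 per arm, the safety conclusion will probably read as inconclusive or descriptive. That is what this sample size can support unless the justified margin is wide.
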